### **Enrollment procedure for patients and family members**

The CMHCs participating in the study are asked to refer all potential cases of psychosis at their first contact with the service over a period of 1 year. The Screening Schedule for Psychosis [15] is administered to all patients as soon as possible after first service contact, and must be administered within 15 days. Inclusion criteria are based on the screening methodology adopted in the WHO 10-country study [15].

In both experimental and control CMHCs, patients meeting all inclusion criteria are invited to undertake standardized assessments as soon as possible once they achieve clinical stabilization (see ‘Baseline assessment’ paragraph). Eligible patients are also asked for consent to involve a key family member in the assessments. An independent, trained researcher conducts the informed consent interview, as approved by the ethics committee of the Coordinating Center at the Academic Hospital of Verona and the local ethics committees. All participants are informed that it is possible to withdraw consent to assessments at any time. If the patient or the family member does not agree to be assessed, the independent researcher briefly records the reasons for refusal, whenever possible. Once informed consent is obtained, independent researchers complete the baseline quantitative assessments for both the participant and the family member. As a minimum, the ‘core’ set of baseline assessments (see ‘Baseline assessment’) are completed before the beginning of treatment (either TAU plus experimental therapy or TAU alone). If the patient is not accessible for baseline assessment (consent given but appointments missed, lack of time, etc.), the interventions begin if possible with the same time schedule, and the core baseline measures are retrospectively reconstructed by consulting the patient’s case record.

From 1 May 2011, a checking procedure using both screening and baseline assessment phases is being undertaken in the CMHCs participating in the study, in order to guarantee the completeness and the accuracy of the recruitment procedure and to identify any missed cases. Generally, this procedure is called the ‘leakage study’ and is considered a fundamental part of pragmatic epidemiologically based trials. All electronic and paper information systems in the CMHCs are carefully scrutinized for any cases aged 18–54 years, presenting to the services for the first time during the index period, ICD-10 diagnostic codes of psychosis (F20-F29, F30.2, F31.2, F31.5, F31.6, F32.3, F33.3, F1x.4; F1x.5, F1x.7, F1x.8, F1x.9). These data are compared with case records to confirm eligibility. This procedure will be completed on 31 January 2012. All identified patients will therefore be invited to participate in the informed consent interview, and the ‘core’ baseline measures (see ‘Baseline assessment’) will be retrospectively reconstructed by consulting the patient’s case record.

### **Baseline assessment**

After clinical stabilization, patients are assessed by independent evaluators with a set of standardized instruments (Table 1) to measure: premorbid IQ (Italian version of the New Adult Reading Test; Test Intelligenza Breve (TIB)) [28], substance abuse (Clinical Drug Use Scale; CDUS) [29], symptoms (Positive and Negative Syndrome Scale; PANSS) [30], (Hamilton Rating Scale for Depression; HAMD) [31], (Bech-Rafaelsen Mania Rating Scale; BRMRS) [32]], global functioning (Global Assessment of Functioning; GAF) [33], subjective appraisal of positive symptoms (Psychotic Symptom Rating Scale; PSYRATS) [34], social disability (Disability Assessment Scale; DAS) [35], insight (Schedule of Assessment of Insight; SAI-E) [36], needs for care (Camberwell Assessment of Needs; CAN-EU) [37], quality of life (World Health Organization Quality of Life; WHOQOL-Bref) [38], life events (first 14 years of life, 1 year before the onset of psychosis and period after onset; *ad hoc* schedule for life events [39]; Childhood Experience of Care and Abuse Questionnaire (CECA-Q) [40]), parental bonding (Parental Bonding Instrument; PBI) [41], and expressed emotions (Level of Expressed Emotion Scale; LEE) [42]. The ‘core’ set of baseline assessments includes PANSS, HAM-D, BRMRS, GAF, and DAS. Patients are also assessed by a set of tests evaluating neuropsychological performance (such as Wisconsin Card Sorting Test (WCST), AX-Continuous Performance Test (AX-CPT), and Wechsler Adult Intelligence Scale (WAIS)).

**Table 1 T1:** Study schedule: instruments used at baseline and follow-up assessments in the Genetics, Endophenotypes and Treatment: Understanding Early Psychosis (GET UP) Psychosis Early Intervention and Assessment of Needs and Outcome (PIANO) trial

	**Enrolment (12 months)**	**Baseline**	**Follow-up (9 months from baseline)**
Patients			
Review of inclusion criteria	X		
Informed consent signed	X		
Consent for involvement of family members	X		
Sociodemographic and clinical data		X	
Instruments			
Core set: PANSS, HAM-D, BRMRS, GAF, DAS		X	X
TIB, Life events (CECA-Q, PBI), neuropsychological tests (WCST, AX-CPT, WAIS)		X	
CDUS, PSYRATS, SAI-E, CAN-EU, WHOQOL-Bref, LEE		X	X
LCS, VSSS-EU			X
SCAN			X
Psychosocial/pharmacological treatment/admissions schedule			X
VITreT			X
Reporting of pharmacological side-effects and other adverse events		X	X
Family members			
Informed consent signed	X		
IEQ-EU, GHQ		X	X
PSA		X	
VSSS-Relatives			X

AX-CPT, AX-Continuous Performance Test; BRMRS, Bech-Rafaelsen Mania Rating Scale; CAN-EU, Camberwell Assessment of Needs; CDUS, Clinical Drug Use Scale; CECA-Q, Childhood Experience of Care and Abuse Questionnaire; DAS, Disability Assessment Scale; GAF, Global Assessment of Functioning; GHQ, General Health Questionnaire; HAM-D, Hamilton Rating Scale for Depression; IEQ-EU, Involvement Evaluation Questionnaire; LCS, Life Chart Schedule; LEE, Level of Expressed Emotion Scale; PANSS, Positive and Negative Syndrome Scale; PBI, Parental Bonding Instrument; PSA, Premorbid Social Adjustment; PSYRATS, Psychotic Symptom Rating Scale; SAI-E, Schedule of Assessment of Insight; SCAN, Schedule for Clinical Assessment in Neuropsychiatry; TIB, Test Intelligenza Breve (Italian version of the New Adult Reading Test); VITreT, Verona Interview for Treatment Termination; VSSS-EU, Verona Service Satisfaction Scale, patient version; VSSS-Relatives, Verona Service Satisfaction Scale, relatives version; WAIS, Wechsler Adult Intelligence Scale; WCST, Wisconsin Card Sorting Test; WHOQOL-Bref World Health Organization Quality of Life.

Participating patients are asked for consent to involve their family members in the trial. If this is given, family members are also asked to provide written informed consent, and are assessed about their burden of care (Involvement Evaluation Questionnaire; IEQ-EU) [43] and emotional distress (General Health Questionnaire; GHQ) [44]. They are also interviewed about the patient’s premorbid adjustment (Premorbid Social Adjustment scale; PSA) [45].

Before starting the assessments, the independent evaluators receive formal training in the use and administration of the instruments, with measurement of their skills and knowledge, and assessment of inter-rater reliability.

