### **Interventions**

#### ***Experimental treatment***

The experimental treatment package is provided by routine public CMHCs, which operate within the Italian National Health Service and consists of TAU (see next paragraph) plus evidence-based additional treatment. Specifically, the additional treatment comprises three main forms of intervention: 1) cognitive behavioral therapy for psychosis (CBTp) for patients; 2) family intervention for psychosis (FIp); and 3) case management (CM).

CBTp is based on the model developed by Kuipers *et al.*[17], Garety *et al.*[18] and Fowler *et al.*[19], and the model has already been evaluated in randomized controlled trials [20]. It is expected that an optimal number of 20–30 CBT sessions per patient will be delivered during a time frame of 9 months, with weekly sessions held during the first 3 months and fortnightly during the following 6 months. Family intervention is based on the model proposed by Leff *et al.*[21] and further developed by Kuipers *et al.*[22]. It consists of an optimal number of 10–15 sessions over 9 months with each individual family: 6 sessions in the first 3 months, and at least 1 session/month during the following 6 months. For case management, every patient/family has a dedicated case manager, who coordinates all planned interventions.

Experimental interventions are expected to begin as soon as the patient is stabilized (clinical stabilization is defined as a condition allowing the patient to collaborate in at least a brief clinical examination) and after he/she has been assessed with the ‘core’ set of baseline measures (see ‘Baseline assessment’ below). Before the start of the trial, professionals using the experimental interventions received specific training programs in CBTp (conducted as part of the scientific aims of the GET UP PIANO Project), FIp, and CM (conducted as part of the scientific aims of the GET UP TRUMPET Project). At the end of the training, an assessment of the competence achieved was performed, and detailed intervention manuals based on international standards were developed and given to the professionals as a standard to be followed for the treatment. Professionals are supported in their clinical work by a team of expert psychotherapists assigned to each CMHC. Moreover, experimental interventions provided to all patients/relatives are supervised by a team of external experts who hold one-day meetings every 2 months and are regularly available for consultation.

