### **Primary outcomes**

The primary outcomes are:

· Changes from baseline to the 9-month follow-up assessment in positive and negative symptom severity and subjective appraisal, as measured by the positive and negative subscales of the PANSS and by the PSYRATS.

· Relapse occurrences during the period between baseline and the 9-month follow-up assessment, where relapse is defined as an episode that has resulted in an admission to a psychiatric inpatient unit (number and days of hospitalization) and/or any case noted record of re-emergence after a period of full/partial remission of positive psychotic symptoms of at least moderate degree requiring a significant change in the clinical management (for example, increased visiting or medication levels) [49]. Consensus ratings will be made by paired members of the research team (blind to the randomization arm) using *a priori* operational definitions.

In this pragmatic trial, two primary outcome measures were defined in order to detect more finely-tuned clinical changes also in those patients (nearly 60%) [50] who are not expected to relapse over the study period, and in those who have a continuous course of illness.

In addition to relapse occurrences, the number of months in full or partial remission will be calculated in a randomly selected subsample of 30% of the participating subjects. This will be obtained by means of a published method for rating remission in psychosis that has been used in previous randomized controlled trials [18,49,50]. Consensus ratings will be made by paired members of the research team using manualized *a priori* operational definitions, a method with good validity and moderate to good reliability [18,49]. Ratings are based on the level of positive psychotic symptoms, and the technique will be applied to detailed extracts of the clinical case notes. These will consist of monthly reports over 9 months on mental state and service interventions, from which all information identifying the location of the clinical service and the nature of treatment will have been removed. Actual group allocation will remain concealed until all ratings are complete. Data on all hospital admissions will be retrieved from the hospital discharge records administrative database.

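### PSYRATS change is part of a primary outcome, but PSYRATS is outside the core set, so its baseline may be taken after treatment starts or not exist

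*Protocol article*

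**What the plan says.** Under Primary outcomes, the first primary outcome is change from baseline to 9 months "in positive and negative symptom severity and subjective appraisal, as measured by the positive and negative subscales of the PANSS and by the PSYRATS". PSYRATS thus stands beside the two PANSS subscales as a primary instrument.

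The Baseline assessment section defines the core set: "The ‘core’ set of baseline assessments includes PANSS, HAM-D, BRMRS, GAF, and DAS". Table 1 agrees. One row reads "Core set: PANSS, HAM-D, BRMRS, GAF, DAS" and PSYRATS sits in a separate row, "CDUS, PSYRATS, SAI-E, CAN-EU, WHOQOL-Bref, LEE", marked at baseline and at follow-up.

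Two sections say what must come before treatment. Under Experimental treatment, the interventions begin once the patient is stable and "after he/she has been assessed with the ‘core’ set of baseline measures". Under Enrollment procedure for patients and family members: "As a minimum, the ‘core’ set of baseline assessments (see ‘Baseline assessment’) are completed before the beginning of treatment". That second sentence covers both arms.

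If a patient cannot be reached for the baseline interview, "the interventions begin if possible with the same time schedule, and the core baseline measures are retrospectively reconstructed by consulting the patient’s case record". The same section applies the same core-only reconstruction to patients identified by the leakage study.

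**The concern.** A change score needs a baseline measured before the treatment it is meant to evaluate. The core set secures this, for directly assessed patients, for PANSS and for four scales that are not the named instruments of either primary outcome (HAM-D, BRMRS, GAF, DAS). It does not secure it for PSYRATS, which is such an instrument.

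Two things follow. A centre can keep to every rule, complete the core set, start treatment and rate PSYRATS later. CBT is weekly for the first 3 months, so a late rating in the experimental arm could already reflect some of it. Second, a patient whose baseline is reconstructed has no PSYRATS baseline by any route the article gives. These are patients who missed appointments or were missed at recruitment, so their absence is unlikely to be random, and they belong to the epidemiologically based cohort the trial sets out to capture.

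At stake is the subjective-appraisal component of the first primary outcome.

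**Working it through.** The article states no figure on this point, so there is none to reproduce. The check compares the rules and then looks at what each gap would do.

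**1. Rules side by side**

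| Rule | PANSS | PSYRATS |
|---|---|---|
| Primary change outcome (Primary outcomes) | yes | yes |
| Marked at baseline and follow-up (Table 1) | yes | yes |
| In the core set (Baseline assessment, Table 1) | yes | no |
| Must precede treatment (Experimental treatment; Enrollment procedure for patients) | yes | no |
| Rebuilt if the patient cannot be assessed (same Enrollment section) | yes | no |
| Rebuilt for leakage-study cases (same Enrollment section) | yes | no |

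The text and Table 1 define the core set identically, so the omission is not a slip in one place.

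**2. Effect of a late baseline**

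Let D be the true between-arm difference in mean improvement. Let p_E and p_T be the shares rated late in the experimental and TAU arms, and g_E and g_T the mean improvement those patients had already made when rated. Each arm's measured improvement falls by p × g, so

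expected difference = D − (p_E × g_E − p_T × g_T).

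- With equal shares p in both arms this is D − p × (g_E − g_T). The difference shrinks if early improvement is greater under CBT.
- With unequal shares the result depends on which product is larger.

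None of p_E, p_T, g_E and g_T is in the article. The direction toward zero is therefore conditional, and the amount cannot be computed.

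**3. Effect of a missing baseline**

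Inputs from Sample size and power calculations: 400 patients and about 10% loss to follow-up, so 400 × 0.90 = 360 with follow-up. Let f be the share without a PSYRATS baseline. It is not stated and is assumed here to be independent of loss to follow-up.

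Patients with a PSYRATS change score = 360 × (1 − f)

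- f = 10%: 324
- f = 20%: 288
- f = 30%: 252
- f = 50%: 180

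These counts apply to an analysis that needs both values. Under Statistical analysis, mixed models are said to accommodate patients whose follow-up data are incomplete. Nothing is said there about a missing baseline.

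**The case against.** The best reply is that a pre-treatment PSYRATS is plainly intended. Table 1 marks it at baseline, the Baseline assessment section lists it among the instruments given after stabilization, and the Enrollment section has researchers complete the baseline assessments once consent is obtained. The core set is a floor and not the plan. This stands as a statement of intent, and nothing shows late rating to be common. It does not close the gap: the binding requirement is the floor, and in the two reconstruction routes PSYRATS is absent by rule.

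Three stronger readings are tempting, and the article does not support them.

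- A reader might infer that late baselines arise only in the experimental arm and so must bias the result toward no effect. The core-only minimum applies to TAU as well, and a late TAU rating also absorbs improvement. Nothing indicates that lateness differs by arm.
- A reader might infer that patients without a PSYRATS baseline necessarily leave the primary analysis. That depends on the model. The article plans random-effects models under a missing-at-random assumption, and the detailed specification may lie in an analysis plan not shown.
- A reader might infer that PANSS is fully protected by contrast. For reconstructed patients PANSS comes from case notes, so they have no direct pre-treatment PANSS rating either.

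It is also fair to say that PSYRATS is one component of one of two primary outcomes, and that the patient sample size rests on relapse and/or severe-symptom rates. That limits the reach of the problem.

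**Conclusion.** The point holds as a gap in the rules. One instrument of a primary change outcome has no guaranteed pre-treatment baseline in either arm, and has no baseline at all for patients whose core measures are reconstructed. The conclusion rests on the text alone.

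Its size is unknown. The article gives neither the timing of PSYRATS relative to treatment start nor the share of reconstructed baselines. A percentage attenuation would rest on invented inputs, so none is offered. The counts of 324 down to 180 are an illustration under assumed shares. Attenuation toward zero is a real possibility if CBT acts early on PSYRATS and late rating is at least as common in the experimental arm, but it is not demonstrated. The gap concerns the PSYRATS component only. It is worth closing because the instrument is already scheduled at baseline and because the handling should be fixed before outcome data are seen.

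**What to change.** **For patients still to be assessed.** Require PSYRATS together with the core set before treatment starts, in both arms, and amend the Baseline assessment section and Table 1 accordingly. State that PSYRATS is exempt from case-note reconstruction; otherwise adding it to the core set would bring it under that rule. The existing provision for patients who cannot be assessed can stay, with their PSYRATS baseline recorded as missing.

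**For patients already enrolled.** Enrolment has run since April 2010 and closes on 31 January 2012, so reordering assessments cannot help them. Classify each PSYRATS baseline as valid or missing by one date rule applied identically in both arms, for example a fixed window from the core baseline assessment, with its length set before outcomes are examined. Do not key the rule to the first CBT or family session: TAU patients have no such sessions, so the arms would be treated differently.

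**For the analysis.** Use a single model of 9-month PSYRATS that retains patients with a missing baseline, for example a constrained longitudinal mixed model with baseline as one of the outcomes and a random effect for cluster. Do not analyse some patients on change and others on the 9-month value, which mixes two quantities in one comparison. This model assumes data missing at random and equal baseline means across randomized arms. Patients are recruited after centres know their allocation, so the second assumption should be checked. Report by arm the number of valid, late and absent PSYRATS baselines.

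**Cost.** A short text change, one date check per patient and a slightly longer pre-treatment interview. No new instrument is needed.

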### **Follow-up assessment**

After a 9-month period from baseline assessment, patients are reassessed to measure: substance abuse (CDUS) [29], symptoms (PANSS [30], HAMD [31], BRMRS [32]), global functioning (GAF) [33], subjective appraisal of positive symptoms (PSYRATS) [34], social disability (DAS) [35], insight (SAI-E) [36], need for care (CAN-EU) [37] and quality of life (WHOQOL-Bref) [38] (Table 1). Patients are also evaluated in terms of pharmacological side-effects and other adverse events, pattern of clinical course (Life Chart Schedule; LCS) [46] and service satisfaction (Verona Service Satisfaction Scale, patient version; VSSS-EU) [47].

Family members are reassessed with respect to burden of care (IEQ-EU) [43] and emotional distress (GHQ) [44], and are also assessed for service satisfaction (VSSS, relatives version; VSSS-Relatives) [47].

The formal best-estimate research diagnosis is assessed at the 9-month follow-up using the item group checklist of the SCAN [16]. All relevant baseline and follow-up information is obtained and reviewed by two independent raters to formulate the ICD-10 diagnosis. In cases where a consensus is not reached, the opinion of a third rater is solicited to clarify diagnostic problems.

Psychosocial and pharmacological treatment, together with number and days of admission provided in the 9-month follow-up period, are recorded in a detailed *ad hoc* schedule.

All patients who have terminated contact with the service before the 9-month follow-up are traced and asked to undergo a semi-structured interview on the characteristics of treatment termination (Verona Interview for Treatment Termination, VITreT). This consists of 10 questions assessing: if the decision to interrupt service contacts was shared or not with the key clinician; the reason for interruption; which type of assistance was eventually received thereafter in other settings, including admission to hospital; and satisfaction with the care provided in these settings [48].

### **Randomization procedure**

In total, 96 units entered the randomization procedure, with equal numbers being allocated to each arm. These units were randomly assigned to one of the two trial arms with a 1:1 allocation rate. The trial statistician (blind to CMHC identity) prepared the sequence of treatments (experimental treatment versus TAU) randomly permuted into blocks of two. The randomization schedule was generated using Stata software (version 11.0; Stata Corp, Corp., College Station, TX, USA), using the ‘ralloc’ command for random allocation of treatments balanced in blocks. Subsequently, arm allocation was disclosed to each CMCH, and the allocation sequence was not altered. One CMHC refused to begin the study immediately after the randomization procedure (Figure 1).

**Figure 1 F1:**
[figure not shown]
Flow diagram of Community Mental Health Centers (CMHCs) and patients in the Genetics, Endophenotypes and Treatment: Understanding early Psychosis (GET UP) Psychosis early Intervention and Assessment of Needs and Outcome (PIANO) trial.

Eligible patients were assigned to treatment (experimental intervention versus TAU) in accordance with the allocation of CMHC pertaining to the catchment area of residence.

